#### **2.4.2.3 Subject Withdrawals**

There will be at least one on-call clinician in each center. They would assess the severe adverse events (SAEs) and then determine whether the participant to continue or terminate the trial. Subjects may leave the study at their own discretion or the investigator may determine whether it is in the best interest of subjects to withdraw from the trial due to worsening of symptoms, or the occurrence of a serious adverse event.

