#### **2.4.1.2 Blinding**

In this study, participants, outcome assessors and statisticians will be blinded to treatment allocation. To ensure all participants being blinded to their group allocation, the placebo naproxen will be prepared by Diao Group Chengdu Pharmaceutical LTD (Chengdu, China) with identical taste, smell and appearance as true naproxen, and the sham acupuncture will produce same stimulation as true acupuncture. Participants of different groups will be treated separately and blinded to which acupuncture method they would receive. For blinding assessment, all participants will be requested to guess whether they received ‘True acupuncture plus placebo naproxen’ or ‘Sham acupuncture plus naproxen’ within five minutes after their treatments at cycles 1.5 and 3.

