#### **2.4.2.4 Subject Recruitment, Screening and Group Assignment**

Two strategies will be used to recruit participants with MRM. One is to recruit participants in outpatient clinics from the four centers mentioned above. The other is to show recruitment posters outside the clinics. Research assistants of each center will preliminarily screen the participants by recording their disease condition, history of the disease and treatment, and the demographic data. Experienced neurologist in each trial center will take charge of the diagnosis of MRM. Potential participants will receive a 3-cycle baseline assessment, during which they have to fill out headache diaries. Eligible participants then will be randomized to acupuncture or medication group. Acupuncturists will be in charge of participant assignment, and the trial procedures. Acupuncturists and neurologists will be responsible for the assessment of safety during treatment, including the acupuncture-related

AEs or medication-related adverse events (AEs). During the trial, independent evaluators of each center will instruct the participants how to fill in their headache diaries. The evaluators will record the data on the case report form (CRF) through the whole trial period. The subject flow was shown in **Figure 1**.

[figure not shown]

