**Figure 3. The schedule of enrollment, interventions, and assessments**

## **2.4.4 Outcomes Measurements**

### **2.4.4.1 Primary Outcome**

The primary outcome will be the change from baseline in average number of migraine days per perimenstrual period over cycles 1-3, assessed using headache diary data(14).

Calculation methods:

Average number of migraine days per perimenstrual period over cycles 1-3 is calculated as the cycle average, equals the total of migraine days during perimenstrual period over cycle 1, cycle 2 and cycle 3 divided by 3.

The frequency and severity of migraine will be based on data from headache diary recorded by participants on baseline (Cycle- -3 to Cycle-0), treatment phase (Cycle-1 to Cycle-3) and follow-up phase (Cycle-4 to Cycle-6). In the diaries, the participants recorded on diary cards with details of their migraine attacks, including the time of headache attack and cease, intensity, frequency, location (the forehead, top, temporal, and back of the head), cause of the headache, concomitant symptoms, and acute pain medications (if any) for each migraine attack. Additionally, participants were required to record information of their menstruation and the dates of receiving acupuncture treatments in their headache diaries. If acute pain medications were taken, participants were required to document the name, dosage, and time of taking the medicine, time of pain relief, and side effects of acute pain medication. In each center, data of headache diaries will be checked by two full-time research assistants first, and then entered into e-headache diary database by two independent data entry clerks. The audited data of e-headache diary will be finally carried forward into effectiveness data by statisticians.

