### **8.1 Statistical Analysis**

The primary study hypothesis is that acupuncture is different from medication in decreasing migraine days for women with MRM. The primary outcome is the change from baseline in average number of migraine days per perimenstrual period over cycles 1-3, assessed using headache diary data. The primary analysis will be intention-to-treat with the last observation carried forward (LOCF) method. Migraine days during perimenstrual period will be

summarized in each treatment group and compared using mixed-effect model.

The following secondary outcomes will be analyzed using the mixed-effect model, *t* test, Wilcoxon rank-sum test, Chi-square test or Fisher's exact test, as appropriate and the intent-to-treat principal:

1. Change from baseline in average number of migraine days per perimenstrual period over cycles 4-6
2. Change from baseline in average number of migraine days per outside perimenstrual period over cycles 1-3 and cycles 4-6
3. Change from baseline in mean migraine hours during perimenstrual period over cycles 1-3 and cycles 4-6
4. Change from baseline in mean migraine hours during outside perimenstrual period over cycles 1-3 and cycles 4-6
5. Change from baseline in mean pain VAS during perimenstrual period over cycles 1-3 and cycles 4-6
6. Change from baseline in mean pain VAS during outside perimenstrual period over cycles 1-3 and cycles 4-6
7. Proportion of participants with at least 50% reduction from baseline in number of migraine days during cycles 1-3 and cycles 4-6
8. Proportion of participants using acute pain medication during cycles 1-3 and cycles 4-6
9. Success rate of blinding at cycle 1.5 and cycle 3

A two-side test with  $p < 0.05$  will be considered significant for all analyses.

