## **Missing data**

Efficacy analyses will be conducted in the intention-to treat (ITT) set, which will include all randomized subjects of whom the migraine days are measured in at least on post-baseline 1 cycle.

Missing data will be imputed by the last observation carried forward (LOCF) method (2). In addition, to examine sensitivity of the LOCF method imputed the missing data, we will perform a sensitivity analysis with multiple imputation method under the missing at random (MAR) assumption (3) for the primary outcome with missing data. Multiple imputations use the observed data to fill in the missing values repeatedly to give rise to multiple “pseudo-complete” datasets. We will impute the missing data 100 times using the following one of methods 1) regression imputation, if data sets with monotone missing patterns, or 2) Markov chain Monte Carlo imputation, if data sets with other patterns. For this we will use the SAS procedure Proc MI process. Each method will give rise to 100 different imputed data sets. We will fit our final model described before to each of these imputed datasets and then compute an overall estimate of the intervention effect as an average of the imputation specific estimates. The standard error of the overall intervention effect estimate will be calculated using Rubin’s formula. SAS procedure Proc MIANALYZE will be used to implement these tasks.

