#### **6.3.4 Analyses for Secondary Outcome**

Efficacy analyses for all secondary outcomes will be performed in the ITT population observed cases, with imputation of missing data using LOCF method.

The mixed-effect model (using baseline value as a covariate, treatment as a fixed effect, and center as a random effect) will also be used for secondary outcomes of the changes from baseline in average number of migraine days per outside perimenstrual period, mean migraine hours during perimenstrual period and outside perimenstrual period, mean pain visual analogue scale (VAS) during perimenstrual period and outside perimenstrual period. For proportion of participants with at least 50% reduction from baseline in number of migraine days and proportion of participants using acute pain medication will be compared between groups using a Chi-square test or Fisher's exact test, as appropriate.

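### Withdrawal for worsening symptoms ends follow-up as well as treatment, so LOCF fills cycles that were lost for reasons tied to the outcome

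*Supplement*

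**What the plan says.** Protocol 2.4.2.3 is the only withdrawal rule. After a serious adverse event a clinician decides whether the woman carries on or her participation ends. She may also leave by her own choice. Separately, the "investigator may determine whether it is in the best interest of subjects to withdraw from the trial due to worsening of symptoms", or because of a serious adverse event. The section does not distinguish stopping treatment from ending data collection, and no readable text plans diaries for women who have withdrawn.

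On missing data, Protocol 8.1 states: "The primary analysis will be intention-to-treat with the last observation carried forward (LOCF) method". SAP 6.3.1 (Missing data) repeats LOCF and adds, as a sensitivity analysis, a "multiple imputation method under the missing at random (MAR) assumption (3) for the primary outcome with missing data". It restricts the efficacy set to "all randomized subjects of whom the migraine days are measured in at least on post-baseline 1 cycle". For the secondary outcomes, which include all of cycles 4-6, SAP 6.3.4 says: "Efficacy analyses for all secondary outcomes will be performed in the ITT population observed cases, with imputation of missing data using LOCF method".

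On who may know the arm, Protocol 2.4.1.2 says "participants, outcome assessors and statisticians will be blinded to treatment allocation". Acupuncturists are not in that list, yet Protocol 2.4.2.4 says "Acupuncturists and neurologists will be responsible for the assessment of safety during treatment". The documents do not say who the investigator is.

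**The concern.** In a migraine-prevention trial, worsening of symptoms is largely what the primary outcome measures. A rule that removes a woman from the trial on that ground creates missing data related to the outcome. If such exits differ by arm, the comparison is biased, and timing sets the direction:

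- **Bad cycle recorded before exit.** LOCF carries it forward, which counts against the arm that loses more women.
- **Exit before the bad cycle is recorded.** LOCF carries forward the better earlier value, which favours that arm.
- **Exit before any post-baseline cycle is recorded.** The woman falls outside the efficacy set in SAP 6.3.1, and no imputation reaches her.

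Balance between arms cannot be taken for granted. The active treatments differ, and nothing prevents someone who knows the allocation from deciding the exit.

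**Working it through.** **1. The plan's allowance for loss.** Protocol 2.4.1.3 needs 68 per group and allows 20% loss: 68 / (1 - 0.20) = 85. The plan enrols 86, or 172 in total, a multiple of the block size of 4. It therefore leaves room for 86 - 68 = 18 women lost per arm for any reason.

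**2. Share of data filled.** A woman who leaves after cycle 1 has 2 of her 3 primary-outcome cycles filled by LOCF, and all of cycles 4-6.

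**3. Formula.** Let q be the excess proportion withdrawn in one arm after a recorded cycle 1, and D the mean gap in days between the carried value and the true later value. The bias in the arm difference is then q x (2/3) x D for cycles 1-3 and q x D for cycles 4-6, which is 1.5 times larger.

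**4. Illustration.** All inputs in this step are assumptions except the 86 per arm.

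- Perimenstrual days per cycle are whole numbers from 0 to 5 (a 5-day window), simulated as rounded, clipped normals for 600,000 women per arm.
- Baseline is the mean of 3 cycles, with latent mean 2.5 or 3.0. Later cycles are 0.7 lower in both arms, so there is no true difference.
- Between-/within-woman SDs are 0.8/0.8, 0.8/1.1, 0.6/1.1 and 1.0/0.8.
- One arm loses 5% or 15% of women in a cycle at or above their own baseline mean; the other loses none. This is 0.05 x 86 = 4.3 to 0.15 x 86 = 12.9 women, within the 18 allowed.
- The estimate is the baseline-adjusted difference in the 3-cycle mean, minus the same estimate on complete data. Plus counts against the arm that loses more women.

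| Case | Method | 5% excess | 15% excess |
|---|---|---|---|
| A. Bad cycle 1 recorded, then exit | LOCF, cycles 1-3 | +0.028 to +0.034 | +0.082 to +0.104 |
| A | Multiple imputation, cycles 1-3 | 0.000 | 0.000 |
| A | LOCF, cycles 4-6 | +0.042 to +0.051 | +0.123 to +0.155 |
| B. Exit in a bad cycle 2, not recorded | LOCF, cycles 1-3 | -0.014 to -0.017 | -0.042 to -0.052 |
| B | Multiple imputation, cycles 1-3 | -0.020 to -0.024 | -0.069 to -0.079 |
| C. Exit in a bad cycle 1, not recorded | Outside the efficacy set | -0.025 to -0.028 | -0.085 to -0.094 |

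The formula agrees with case A: 0.104 / (0.15 x 2/3) gives D of about 1.0 day, and 0.15 x 1.0 = 0.15 for cycles 4-6.

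**5. What the sensitivity analysis repairs.** Multiple imputation removes the bias in case A if arm, baseline and recorded cycles are in the imputation model; SAP 6.3.1 does not list the variables. It does not repair case B, and case C lies outside it. It is not planned for cycles 4-6.

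**6. No benchmark.** These figures are not set against the 2.1-day planning difference (5.2 - 3.1). Protocol 2.4.1.3 states that difference over 12 weeks and does not say that it is perimenstrual.

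**The case against.** The strongest reply is that the withdrawal clause is permissive and that other text allows for women who do not complete treatment. SAP 6.3.5 analyses receipt of at least 80% of planned treatment, SAP 6.2 and 6.3.3 define a per-protocol set, SAP 6.2 opens by including everyone randomized, and Protocol 2.4.2.4 has evaluators recording data throughout. The consent text and flow figures cannot be seen and might cover data after withdrawal. This limits the point to what the readable text provides. None of those passages says that a withdrawn woman continues her diary.

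Worsening may also mean intensity, duration or attacks outside the perimenstrual window, and Protocol section 3 lists aggravation of existing symptoms among acupuncture-related adverse events. The overlap with the primary outcome is therefore incomplete, though likely.

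Cases B and C are narrower than case A. Women keep the diary attack by attack, so worsening will often be recorded before exit, and the planned imputation can then handle it for the primary outcome. Case C also depends on which analysis-set definition is followed, since SAP 6.2 and 6.3.1 differ.

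Materiality is fairly challenged. No imbalance is shown, the illustration puts all such loss in one arm, and its trigger includes cycles no better than baseline. The unblinding route is possible but not demonstrated.

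Last, continued diaries cannot help where a woman withdraws consent to data collection. Diaries kept after stopping may also include time on another preventive drug. Using them is a choice of treatment effect, but it fits the intention-to-treat principle stated in SAP 6.2.

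**Conclusion.** The concern holds. As written, the rule turns worsening into loss of follow-up, and LOCF fills the gap. The planned imputation repairs part of this for the primary outcome and none of it for cycles 4-6. On the assumed inputs, the primary comparison shifts by at most about 0.10 days per perimenstrual period under LOCF, and by about 0.09 in the other direction through exclusion from the efficacy set. Cycles 4-6 shift by at most about 0.16. The bias is about zero if loss is equal in both arms. The actual size and sign cannot be derived from the documents. This supports a recommended change, not an essential one, with medium confidence. It rests on the readable text being silent about diaries after withdrawal.

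**What to change.** Amend Protocol 2.4.2.3 to separate (a) stopping acupuncture, tablets or both from (b) leaving the study. A woman who stops for worsening, an adverse event or her own choice should keep the headache diary, acute-medication and adverse-event records through cycle 6, unless she withdraws consent to data collection. Worsening may end treatment but not data collection. Record the date, the reason, the component stopped and who decided. State in the SAP that diary data after stopping enter the primary analysis and the cycles 4-6 outcomes. Clinicians keep full discretion over who stops treatment and when.

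The cost is a short amendment, a small addition to the CRF and modest effort to retain women who have stopped treatment. The diary already runs through cycle 6 in the schedule, and Protocol 2.4.4.1 already provides that "data of headache diaries will be checked by two full-time research assistants first".

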#### **2.4.2.4 Subject Recruitment, Screening and Group Assignment**

Two strategies will be used to recruit participants with MRM. One is to recruit participants in outpatient clinics from the four centers mentioned above. The other is to show recruitment posters outside the clinics. Research assistants of each center will preliminarily screen the participants by recording their disease condition, history of the disease and treatment, and the demographic data. Experienced neurologist in each trial center will take charge of the diagnosis of MRM. Potential participants will receive a 3-cycle baseline assessment, during which they have to fill out headache diaries. Eligible participants then will be randomized to acupuncture or medication group. Acupuncturists will be in charge of participant assignment, and the trial procedures. Acupuncturists and neurologists will be responsible for the assessment of safety during treatment, including the acupuncture-related

AEs or medication-related adverse events (AEs). During the trial, independent evaluators of each center will instruct the participants how to fill in their headache diaries. The evaluators will record the data on the case report form (CRF) through the whole trial period. The subject flow was shown in **Figure 1**.

[figure not shown]

**Figure 1. Subject flow**

### 2.4.3 Trial flow Chart

The trial flow chart and the schedule of enrollment, interventions, and assessments were shown in **Figure 2** and **Figure 3**.

[figure not shown]

**Figure 2. Trial flow chart**

|                                        | STUDY PERIOD |            |           |         |       |           |    |    |
|----------------------------------------|--------------|------------|-----------|---------|-------|-----------|----|----|
|                                        | Baseline     | Allocation | Treatment |         |       | Follow-up |    |    |
| VISIT                                  | 1            | 0          | 2         | 3       | 4     | 5         | 6  | 7  |
| TIMEPOINT(C, cycle)                    | -3-0C        |            | 1C        | 2C      | 3C    | 4C        | 5C | 6C |
| Enrollment                      |              |            |           |         |       |           |    |    |
| Screening                              | ×            |            |           |         |       |           |    |    |
| Informed consent                       | ×            |            |           |         |       |           |    |    |
| Eligibility criteria                   | ×            |            |           |         |       |           |    |    |
| Demography
Characteristics          | ×            |            |           |         |       |           |    |    |
| Disease history of MRM                 | ×            |            |           |         |       |           |    |    |
| Laboratory test                        | ×            |            |           |         | ×     |           |    |    |
| Randomization                          |              | ×          |           |         |       |           |    |    |
| Interventions                   |              |            |           |         |       |           |    |    |
| True acupuncture plus placebo naproxen |              |            | ×         | ×       | ×     |           |    |    |
| Sham acupuncture plus true naproxen    |              |            | ×         | ×       | ×     |           |    |    |
| Assessments                     |              |            |           |         |       |           |    |    |
| Headache diary                         | ×            |            | ×         | ×       | ×     | ×         | ×  | ×  |
| Migraine days                          | ×            |            | ×         | ×       | ×     | ×         | ×  | ×  |
| Migraine hours                         | ×            |            | ×         | ×       | ×     | ×         | ×  | ×  |
| VAS                                    | ×            |            | ×         | ×       | ×     | ×         | ×  | ×  |
| ≥ 50% migraine responder rate          | ×            |            | ×         | ×       | ×     | ×         | ×  | ×  |
| Intake of acute pain medication        | ×            |            | ×         | ×       | ×     | ×         | ×  | ×  |
| Assessment of blinding                 |              |            |           | ×(1.5C) | ×(3C) |           |    |    |
| Participant's compliance               |              |            | ×         | ×       | ×     |           |    |    |
| Adverse events                         | ×            | ×          | ×         | ×       | ×     | ×         | ×  | ×  |

MRM: menstrually related migraine; VAS: visual analogue scale.

**Figure 3. The schedule of enrollment, interventions, and assessments**

## **2.4.4 Outcomes Measurements**

### **2.4.4.1 Primary Outcome**

The primary outcome will be the change from baseline in average number of migraine days per perimenstrual period over cycles 1-3, assessed using headache diary data(14).

Calculation methods:

Average number of migraine days per perimenstrual period over cycles 1-3 is calculated as the cycle average, equals the total of migraine days during perimenstrual period over cycle 1, cycle 2 and cycle 3 divided by 3.

The frequency and severity of migraine will be based on data from headache diary recorded by participants on baseline (Cycle- -3 to Cycle-0), treatment phase (Cycle-1 to Cycle-3) and follow-up phase (Cycle-4 to Cycle-6). In the diaries, the participants recorded on diary cards with details of their migraine attacks, including the time of headache attack and cease, intensity, frequency, location (the forehead, top, temporal, and back of the head), cause of the headache, concomitant symptoms, and acute pain medications (if any) for each migraine attack. Additionally, participants were required to record information of their menstruation and the dates of receiving acupuncture treatments in their headache diaries. If acute pain medications were taken, participants were required to document the name, dosage, and time of taking the medicine, time of pain relief, and side effects of acute pain medication. In each center, data of headache diaries will be checked by two full-time research assistants first, and then entered into e-headache diary database by two independent data entry clerks. The audited data of e-headache diary will be finally carried forward into effectiveness data by statisticians.

